### Statistical Analysis

Statistical analysis will be performed using SPSS version 21 (IBM Corp). The mean and standard deviation will be calculated and reported for basic patient-related data. Primary analysis will be carried out comparing frequency of reintervention between the intervention and control groups. Moreover, we will try to identify risk factors as basic patient-related data or surgery-associated factors (time of surgery, operation time, experience of the surgeon) using regression models.

Secondary clinical outcome measures will be presented in means with the corresponding standard deviation. The intervention group and the control group will be compared using mean value analysis models (*t* test; multifactorial mean value analysis). We will assume that data missing will be random; therefore, missing data will not be imputed, as we will use the mixed model approach for the longitudinal analyses.

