**Methods:**

In a prospective, randomized controlled, single-blinded, single-center trial based on a noninferiority design, we will enroll 128 patients randomized to either the control or the intervention group. The control group will be treated according to our current, standard protocol in which all patients receive a sterile wound irrigation performed by a home-care service twice a day. Patients randomized to the intervention group will be treated with a nonsterile wound irrigation (shower) twice a day. All patients will have a routine clinical control visit after 1, 3, 6, and 12 weeks in the outpatient clinic. Primary outcome is the reinfection and reoperation rate due to insufficient wound healing diagnosed either at the outpatient control visit or during general practitioner visits. Secondary outcome measures include a Short Form Health Survey, Visual Analog Scale, Patient and Observer Scar Assessment Scale, Vancouver Scar Scale, and the EurolQol 5-Dimension Questionnaire. Those questionnaires will be completed at the outpatient control visits.

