### Outcome

As we present a noninferiority approach, the purpose of this analysis is to show comparable results in the intervention group in terms of reinfection and reoperation rates.

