#### Primary Outcome

We defined the primary endpoint as a reinfection or a reoperation after an abscess is surgically drained. A reinfection was defined as a persisting or new reddened wound with signs of induration and fluctuation. If there were any signs of purulent exudation with the above-mentioned signs, we considered the wound to be reinfected, and a reoperation was performed. A reoperation was defined as any operation performed in the same region within the time frame of the study control (12 weeks postoperative).

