### Sample Size Calculation

Based on international publications, we estimate a 15% reinfection rate as statistically significant [20-22]. The literature remains inconsistent concerning reinfection rates in surgically drained abscesses. Based on these findings and using a power of 0.80 and alpha failure of .05 we performed a sample size calculation. Based on a noninferiority approach, we calculated 58 patients were needed in each treatment arm. We added 10% loss of follow-up to our power calculation (58×1.10=64 patients in each treatment arm) and determined 128 patients need to be included in our study.

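### The primary analysis counts only reinterventions, while the primary endpoint is reinfection or reoperation and the sample size rests on a reinfection rate

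*Protocol article*

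**What the plan says.** Three sections of the protocol article name three different primary variables.

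- Primary Outcome: "We defined the primary endpoint as a reinfection or a reoperation after an abscess is surgically drained". This is a composite. The Outcome section ("the purpose of this analysis is to show comparable results in the intervention group in terms of reinfection and reoperation rates") and the abstract ("Primary outcome is the reinfection and reoperation rate due to insufficient wound healing") also name both components.
- Sample Size Calculation: "we estimate a 15% reinfection rate as statistically significant". This is reinfection alone.
- Statistical Analysis: "Primary analysis will be carried out comparing frequency of reintervention between the intervention and control groups". This is reintervention alone.

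Reinfection is described in two sentences under Primary Outcome. The first is "A reinfection was defined as a persisting or new reddened wound with signs of induration and fluctuation". The second is "If there were any signs of purulent exudation with the above-mentioned signs, we considered the wound to be reinfected, and a reoperation was performed". Reoperation is defined there as any operation in the same region during the 12 weeks of follow-up. The design is noninferiority throughout, but the article gives no numerical margin.

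**The concern.** The variable in the primary analysis is narrower than the endpoint. Under the first reinfection sentence, a red, indurated and fluctuating wound is an event, and pus is not mentioned. Reoperation is stated only for wounds that also show purulent exudation. A wound that meets the first sentence and is not reoperated therefore counts towards the endpoint but not in the analysis.

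In a noninferiority trial this can affect the conclusion. If both arms lose the same share of events and the margin is a fixed number of percentage points, the observed difference shrinks while the margin does not. An intervention that is worse by the full margin on the defined endpoint would then pass more often than the nominal error rate allows.

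**Working it through.** **1. Is reintervention shorthand for the composite?** The abstract (Background and Conclusions) and the Introduction each list reinfection and reintervention side by side as two rates. In this article's own usage the words are not synonyms, so the plain reading of the analysis sentence leaves reinfection out.

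**2. The plan's own sample size.** Inputs from Sample Size Calculation: 15%, power 0.80, alpha .05, 58 per arm. Sidedness and margin are not given. The usual noninferiority formula with equal rates p and margin d is

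n = 2p(1 − p)(z₁₋α + z₀.₈₀)² / d².

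- With 15% as both rate and margin and one-sided .05: 2 × 0.15 × 0.85 × (1.645 + 0.842)² / 0.15² = 70.1, so 71 per arm. At one-sided .025 it is 89.
- 58 is therefore not reproduced by this reading. Solving for d with p = 0.15 and n = 58 gives √(0.255/58) × (1.645 + 0.842) = 0.165 at one-sided .05, and 0.186 at .025.
- The inflation reproduces as written: 58 × 1.10 = 63.8, so 64 per arm and 128 in total.

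The 16.5-point margin used below is thus back-solved from 58 and is an assumption.

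**3. Consequence of losing events.** Assumptions not in the article: margin 16.5 points, true composite rates 15% (control) and 31.5% (intervention), and a share f of composite events reoperated, equal in both arms. The reintervention rates are then 0.15f and 0.315f, and their difference is 0.165f. Noninferiority is declared when the Newcombe one-sided 95% upper limit for intervention minus control,

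(p_T − p_C) + √[(u_T − p_T)² + (p_C − l_C)²],

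lies below 0.165, where u and l are Wilson limits. Exact binomial enumeration with 58 per arm gives:

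| Share reoperated, f | True difference in reinterventions | False noninferiority |
|---|---|---|
| 1 (no loss) | 16.5 points | 5.3% |
| 0.90 | 14.9 points | 8.0% |
| 0.80 | 13.2 points | 12.0% |
| two-thirds | 11.0 points | 20% |
| 0.50 | 8.3 points | 38% |

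With a 15-point margin and true rates of 15% and 30%, the same series is 5.2%, 7.6%, 11%, 19% and 34%. The pattern does not depend on the exact margin.

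**4. Sensitivity to the two assumptions that drive the direction.**

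- Unequal loss: if 50% of control events and 80% of intervention events are reoperated, the rates are 0.15 × 0.50 = 7.5% and 0.315 × 0.80 = 25.2%. False noninferiority is then 3.5%, below nominal. At 50% and 90% it is 1.2%.
- Margin scaled to the narrower outcome (0.165f instead of 0.165): the rate stays at about 5% for every f tried.

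**5. What the trial has seen so far.** The Results section reports 2 reoperations and 1 change of treatment (antiseptic therapy) among 50 enrolled patients. The third patient is not said to have had a reinfection. The reoperated share is 2 of 2 or 2 of 3, too few to estimate f.

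**The case against.** The strongest reply is that few or no events may be lost. The second reinfection sentence ties a purulent, reinfected wound to reoperation. The first requires fluctuation, which the Defining Period section attributes to a collection of liquefied tissue, that is, pus. On that reading reinfection and reoperation nearly coincide, and the analysis sentence is only loosely worded. This stands as a limit on the size of the problem: the low end of the range in the table is as credible as the high end. It does not remove the mismatch. If every reinfection is reoperated, the reinfection half of the composite adds nothing, and the article still names different variables for endpoint, sample size and analysis.

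A reader might infer that the analysis as written always favours a false finding of comparability. The article does not support that. It holds only with similar loss in both arms and a fixed absolute margin, and step 4 shows cases where it fails.

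A reader might also infer that noninferiority will be claimed from a nonsignificant difference test. The article names no test for the primary outcome. The test, the interval and the analysis sets may stand in an analysis plan that is not shown, so no finding is made on them.

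**Conclusion.** The point holds as an internal contradiction: the Statistical Analysis section analyses reintervention, the Primary Outcome section defines reinfection or reoperation, and the Sample Size Calculation uses a reinfection rate. This conclusion needs no assumption.

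The size of the consequence does need assumptions. With 58 per arm, a fixed 16.5-point margin, true rates of 15% and 31.5%, one-sided .05 and equal loss, false noninferiority runs from about 5% (no loss) to 38% (half of events not reoperated), with 8%, 12% and 20% in between. The article gives neither the margin nor the reoperated share, so no single value in that range can be claimed, and unequal loss could reverse the direction. The mismatch should be corrected before the analysis because it decides which events determine the trial's conclusion.

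**What to change.** 1. In Statistical Analysis, make the primary analysis variable the defined composite, reinfection or reoperation within 12 weeks. Assess it as the difference in proportions between arms, with a confidence interval compared with the noninferiority margin.
2. In Sample Size Calculation, write out the margin that was used, with the assumed rate and the sidedness of alpha. The comparison in item 1 cannot be carried out without it.
3. Report reinfection and reoperation separately as supportive components.
4. In Primary Outcome, reconcile the two reinfection sentences so that it is clear which wounds count as events and whether a reinfection without reoperation is possible. Which reading is right is for the trial team to decide.

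The cost is a text change in three sections and agreement on the event definition. No new data are needed: blinded surgeons already record cellulitis, exudation and persisting fluctuation at the control visits. With 50 of 128 patients enrolled at publication, the change could be made before the analysis.

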#### Defining Period

Standard preoperative documentation of the abscess and its surrounding is necessary to ensure sufficient surgical drainage and to enable comparability between both groups. An abscess was defined as an enclosed collection of liquefied tissue, known as pus, affecting the subcutaneous tissue and representing the immune defense reaction of the body against foreign material or bacteria. As seen in Figure 1, the abscess consists of (1) the area of fluctuation caused by the collection of liquefied tissue, (2) the area of cellulitis caused by hyperemia due to an immune reaction of the body, and (3) the area of induration caused by the hardening of the soft tissue due to the inflammation.

We also defined provisions that needed to be followed to ensure proper surgical drainage during our trial: (1) the incision of the skin has to be at least as long as the fluctuation, (2) the incision of the skin has to be spindle-shaped to ensure a wide opening of the abscess cavity, and (3) the spindle-shaped incision has to include at least two-thirds of the width of the fluctuation.

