#### Implementation Period

An educational period teaching basic facts about abscesses will be initiated before the inclusion period starts. All surgeons treating the above mentioned conditions will participate in a special lecture about the pathophysiology, diagnosis, and management of abscesses. We defined the necessity for documentation of the following parameters (see Figure 1): the diameter of the fluctuation and hyperemia and photo documentation with a scale. Finally, everyone involved received handouts containing all relevant information.

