### Randomization

Prior to the operation, patients are being randomized either to the control or the intervention group using sealed envelopes. The randomization will be carried out after the signed informed consent is obtained.

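### Preoperative abscess diameter is recorded partly to make the groups comparable, but no treatment comparison is committed to using it: a cheap, low-severity gain in precision and prespecification for the scar and wound outcomes

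*Protocol article*

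**What the plan says.** All references are to the protocol article.

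- **Purpose of the measurement (Defining Period).** "Standard preoperative documentation of the abscess and its surrounding is necessary to ensure sufficient surgical drainage and to enable comparability between both groups". The drainage rules in the same section tie the wound to the measurement: "the incision of the skin has to be at least as long as the fluctuation", and the opening must also take in at least two-thirds of the fluctuation's width.
- **What is recorded (Implementation Period).** "the diameter of the fluctuation and hyperemia and photo documentation with a scale".
- **Allocation (Randomization).** "patients are being randomized either to the control or the intervention group using sealed envelopes". Nothing is said about blocks or strata.
- **Primary comparison (Statistical Analysis).** "Primary analysis will be carried out comparing frequency of reintervention between the intervention and control groups". No covariate is named.
- **Regression (Statistical Analysis).** A separate search for risk factors draws on "basic patient-related data or surgery-associated factors (time of surgery, operation time, experience of the surgeon) using regression models". Abscess size is not among the three surgical factors listed.
- **Secondary comparison (Statistical Analysis).** "The intervention group and the control group will be compared using mean value analysis models". The sentence ends with a bracket that names a t test and a multifactorial comparison of means, without saying which factors enter or which result counts. A mixed model is announced for the longitudinal data.
- **Timing (Outpatient Control Visits, Table 1).** VSS and POSAS are taken once, at week 12. The medical questionnaire, which records the size of the wound cavity, is completed at several visits.

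**The concern.** The trial standardises one preoperative measurement and gives group comparability as one of its two reasons. By the trial's own drainage rule, that measurement also sets a lower limit on the wound. It is taken before the operation, so the aftercare cannot change it. VSS and POSAS are measured only at week 12, so the longitudinal mixed model does not serve them and they have no baseline value to adjust for. Fluctuation diameter is then the obvious covariate.

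The analysis text is not simply silent on factors. It lists three surgical ones for a risk-factor search and leaves this one out. For the scar scores it offers an adjusted and an unadjusted method together and ranks neither.

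Two things are at stake, both modest. The first is precision on secondary outcomes, which could be had from data already collected. The second is freedom to choose between an adjusted and an unadjusted scar result after both have been seen.

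**Working it through.** **Inputs.** From Sample Size Calculation: 58 patients per arm before loss to follow-up, inflated as 58 × 1.10 = 63.8, rounded to 64, and 2 × 64 = 128 in total. That inflation reproduces as written. The 58 itself cannot be derived uniquely, because no margin is stated and the role of the 15% is unclear. It serves here only as the number of evaluable patients per arm. *Assumed:* the correlation r between diameter and a scar score, and the odds ratio per SD of diameter for the primary outcome. The article gives neither.

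**1. Size of a chance imbalance.** The standard error of the difference in mean diameter is √(2/58) = 0.186 SD. The 95% range is ±1.96 × 0.186 = ±0.36 SD. The average absolute imbalance is 0.186 × 0.80 = 0.15 SD.

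**2. What it does to a scar score.** The shift is r × imbalance:
- average imbalance: 0.3 × 0.15 = 0.04 SD to 0.5 × 0.15 = 0.07 SD;
- edge of the 95% range: 0.3 × 0.364 = 0.11 SD to 0.5 × 0.364 = 0.18 SD.

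**3. Is the unadjusted test still valid?** Yes. The standard error of a randomised comparison already allows for such imbalances. Simulated type I error of the unadjusted two-sided 5% t test, 58 per arm, was 0.051 (r = 0.3), 0.055 (r = 0.5) and 0.048 (r = 0.7). For an unadjusted noninferiority test with an assumed 15-point margin, nominal one-sided 0.05 and control rates of 12% or 15%, it was 0.054 to 0.058. It was 0.055 to 0.056 when size had no effect at all, so the slight excess over 0.05 does not come from abscess size.

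**4. What adjustment gains on a scar score.** The variance falls by r², the standard error is multiplied by √(1 − r²), and the equivalent gain in patients is 1/(1 − r²) − 1. Power is shown for an illustrative difference of 0.5 SD, as Φ(0.5 / [0.186 × √(1 − r²)] − 1.96).

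| r (assumed) | Variance reduction | SE ratio | Equivalent extra patients | Power, unadjusted → adjusted |
|---|---|---|---|---|
| 0.1 | 1% | 0.99 | 1% | 0.77 → 0.77 |
| 0.3 | 9% | 0.95 | 10% | 0.77 → 0.81 |
| 0.5 | 25% | 0.87 | 33% | 0.77 → 0.87 |

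**5. Primary outcome.** Take 15% as an illustrative event rate. The shift in the risk difference is about p(1 − p) × ln(OR) × imbalance. At the average imbalance this is 0.1275 × 0.405 × 0.15 = 0.8 points (OR 1.5) to 0.1275 × 0.693 × 0.15 = 1.3 points (OR 2.0). The standard error of the risk difference is √(2 × 0.1275/58) = 6.6 points. In simulation the SD of the risk difference was 6.58 points unadjusted and 6.51 standardised over diameter (OR 1.5), and 6.55 and 6.40 (OR 2.0). The gain is negligible.

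**6. Events available.** At 15%, 0.15 × 116 = 17 events. The Results section reports 2 reoperations among the 50 patients enrolled so far, so there may be fewer. A model for the primary outcome should carry no more than this one covariate.

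**The case against.** The strongest reply is that this is an omission and not an error. Covariate lists are commonly left to a full protocol or analysis plan, and neither is shown. The sentence on secondary outcomes names a multifactorial analysis, which may well include abscess size, and the mixed model could already cover wound-cavity size. The preoperative documentation also serves adequate drainage, and reporting size by group in a baseline table would go some way to meeting the comparability aim. Most scar items are not about size: by the article's own description, VSS scores vascularity, height or thickness, pliability and pigmentation, and only the observer part of POSAS includes surface area. The correlation may therefore be below 0.3, and then little is gained.

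Much of this stands. It cannot be said that the scar comparison is unadjusted, only that the article does not fix whether it is. The gain rests on an assumed correlation, and at r = 0.1 it is 1%. What the reply does not remove is that the article does set out methods and factors, places an adjusted and an unadjusted comparison side by side without ranking them, and commits to no use of a measurement it calls necessary. If a separate analysis plan names the diameter and the decisive model, the point is met.

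**Conclusion.** The point holds as a free or cheap improvement of low severity. The article collects preoperative fluctuation diameter partly for comparability and does not commit to it in any treatment comparison. The cost is precision on the secondary wound and scar outcomes: 9 to 25% of the variance of a scar score if r is 0.3 to 0.5, an assumption for which the article offers no figure. The choice between adjusted and unadjusted results is also left open.

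A reader might infer three stronger things that the article does not support:

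- **That chance imbalance in abscess size enters the results uncorrected and biases them.** Randomisation and the standard error already account for it, the simulated error rates stayed close to nominal, and a multifactorial analysis and a mixed model are planned.
- **That the allocation is at fault for not stratifying by size.** The article mentions only sealed envelopes. Its silence on strata is detail that an article may leave out.
- **That the reinfection or reoperation result is distorted.** The likely shift is about 1 point against a standard error of 6.6 points, and adjustment barely changes the precision.

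**What to change.** In Statistical Analysis:

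1. State that VSS and both POSAS scales at week 12 are compared by analysis of covariance with arm and preoperative fluctuation diameter, in place of the t test.
2. Include the diameter as a covariate in the mixed model for wound-cavity size at follow-up.
3. Keep the unadjusted risk difference as the main primary result. Add, as a prespecified supportive analysis, the risk difference standardised over fluctuation diameter, with that one covariate only because events are few.
4. Give a simple rule for a missing diameter, such as reading it from the scaled photograph.

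The cost is a few sentences and a little more analysis work. Enrolment, treatment and follow-up do not change, and the data are already required. If diameter turns out unrelated to the scar scores, the loss is one degree of freedom out of 114 (2 × 58 − 2).

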### Sample Size Calculation

Based on international publications, we estimate a 15% reinfection rate as statistically significant [20-22]. The literature remains inconsistent concerning reinfection rates in surgically drained abscesses. Based on these findings and using a power of 0.80 and alpha failure of .05 we performed a sample size calculation. Based on a noninferiority approach, we calculated 58 patients were needed in each treatment arm. We added 10% loss of follow-up to our power calculation (58×1.10=64 patients in each treatment arm) and determined 128 patients need to be included in our study.

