## Abstract

**Background:**

Skin abscesses are a frequent encountered health care problem and lead to a significant source of morbidity. They consequently have an essential impact on the quality of life and work. To date, the type of aftercare for surgically drained abscesses remains under debate. This leads to undesirable practice variations. Many clinical standard protocols include sterile wound dressings twice a day by a home-care service to reduce the chance of a recurrent wound infection. It is unknown, however, whether reinfection rates are comparable to adequate wound irrigation with a nonsterile solution performed by the patient. Our hypothesis is that simple wound irrigation with nonsterile water for postoperative wound care after an abscess is surgically drained is feasible. We assume that in terms of reinfection and reintervention rates unsterile wound irrigation is equal to sterile wound irrigation.

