## Methods

### Study Design

Based on a noninferiority design, we designed a prospective, randomized, controlled, single-blinded, single-center trial. We present the study protocol in accordance with the Standard Protocol Items: Recommendations for Interventional Trials guidelines [15].

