## Results

The trial was started in June 2016 and enrolled 50 patients by article publication. Regarding the adherence to our protocol, we found 10% of loss of follow-up until now. Only 2 patients needed reoperation and only 1 patient needed a change of treatment (antiseptic therapy). Most patients are happy with their randomized treatment but as expected some patients in the sterile group complained about timing problems with their working hours and home-care service appointments. Most patients in the nonsterile group are satisfied being able to take care of their wounds independently although some patients still depend on the home-care service for the wound dressing.

We are hoping to have enrolled enough patients by summer 2017. The follow-up will take until autumn 2017, and study results are expected to be published by the end of 2017. This trial is solely supported by the cantonal hospital of Lucerne.

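### The noninferiority sample size states no margin, and its one effect input is mislabelled, so 58 per arm and 80% power cannot be verified

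*Protocol article*

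**What the plan says.** The Study Design section makes the trial a noninferiority trial: "Based on a noninferiority design, we designed a prospective, randomized, controlled, single-blinded, single-center trial". The Abstract gives the hypothesis as equality: "We assume that in terms of reinfection and reintervention rates unsterile wound irrigation is equal to sterile wound irrigation". The Outcome section puts the aim this way: "the purpose of this analysis is to show comparable results in the intervention group in terms of reinfection and reoperation rates". None of these attaches a number to the difference that could be tolerated.

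The primary endpoint is a composite of reinfection or reoperation, with reoperations counted up to 12 weeks. The Statistical Analysis section says that the primary analysis compares the frequency of reintervention between arms. It names no margin and no confidence-limit rule.

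The Sample Size Calculation section has one effect input: "Based on international publications, we estimate a 15% reinfection rate as statistically significant [20-22"]. It adds power 0.80 and alpha .05, without sidedness, and concludes: "Based on a noninferiority approach, we calculated 58 patients were needed in each treatment arm". A 10% allowance for loss follows, "58×1.10=64 patients in each treatment arm", which makes 128 in total.

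**The concern.** Statistical significance is a property of a test result, so an estimated rate cannot have it. The sentence leaves open whether 15% is the expected rate, the margin or a difference between arms. A noninferiority sample size needs at least an expected rate and a margin, and only one number is given.

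Two things are at stake. First, a reader cannot tell what the trial has 80% power to show. Second, as this document reads, nothing says what result would count as success. The article ties a change in aftercare, and the projected saving, to a comparable result. If the margin is not fixed in advance, it could be chosen after the results by arm are known.

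**Working it through.** **Inputs from the protocol article.** Rate 15% (role unclear), power 0.80, alpha .05 (sidedness not given), 58 per arm, loss 10%. The margin and the expected rate in the intervention arm are not given. I take the rate as equal in both arms, following the hypothesis in the Abstract.

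**Formula.** With common rate p, absolute margin d and unpooled variance, n per arm = (z_α + z_β)² × 2p(1−p) / d². With z_β = 0.8416:
- one-sided .05: (1.6449 + 0.8416)² = 6.183
- one-sided .025: (1.9600 + 0.8416)² = 7.849

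**Step 1: try to reproduce 58 from the stated inputs alone.** The only way to run the formula without adding a number is to use 15% twice, as rate and as margin. Then 2p(1−p) = 2 × 0.15 × 0.85 = 0.255 and d² = 0.0225.
- one-sided .05: 6.183 × 0.255 / 0.0225 = 70.07, so 71 per arm
- one-sided .025: 7.849 × 0.255 / 0.0225 = 88.95, so 89 per arm

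Other standard methods move further from 58. At the same two alpha levels, a continuity correction gives 83 and 102, the Farrington-Manning variance 75 and 95, and two one-sided equivalence tests 98 and 120.

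**Step 2: what would give 58?**
- Hold the rate at 15% and solve for the margin, d = (z_α + z_β) × √(0.255/58), where √(0.255/58) = 0.0663. This gives 2.4865 × 0.0663 = 0.165 at one-sided .05, and 2.8016 × 0.0663 = 0.186 at .025.
- Hold the margin at 15 points and solve for the rate, p(1−p) = 58 × 0.0225 / (2 × 6.183) = 0.1055, so p = 12.0%. At .025, p(1−p) = 0.0831, so p = 9.2%.

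Other pairs come close too. A 5% rate with a 10-point margin gives 59 at one-sided .05. Each of these routes needs a number that the article does not state.

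**Step 3: power of 58 evaluable per arm under assumed inputs.** Power = Φ(d / √(2p(1−p)/58) − z_α). The margins below are assumptions to show the range, and the rate is taken as 15% in both arms.

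| Assumed margin | Power, one-sided .05 | Power, one-sided .025 |
|---|---|---|
| 5 points | 19% | 11% |
| 10 points | 45% | 33% |
| 15 points | 73% | 62% |
| 20 points | 92% | 86% |

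For the 15-point row, 0.15 / 0.0663 = 2.262. Then Φ(2.262 − 1.645) = 0.73 and Φ(2.262 − 1.960) = 0.62.

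**Step 4: loss allowance.** 58 × 1.10 = 63.8, rounded to 64, as printed. If 10% of 64 are lost, 64 × 0.90 = 57.6 remain, just under 58. Dividing gives 58 / 0.90 = 64.4, so 65. The gap is one patient per arm.

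**The case against.** The strongest reply is that this is a condensed article. The ethics committee approved the study, and the fuller protocol, which is not shown, may hold the margin. That stands as far as it goes: the point concerns this document and does not show that no margin was ever set. It does not excuse the paragraph, which prints a calculation with power, alpha, number per arm and loss allowance, and mislabels the input on which the rest depends.

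A second reply is that 58 can be correct. This stands. A 15-point margin with a 12.0% rate (9.2% at one-sided .025) yields it, and using 15% as both rate and margin is a reading the article never states. The gap between 58 and 71 or 89 is therefore not an arithmetic error.

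Three stronger readings are tempting, and the document supports none of them.
- **That the design would accept a doubling of reinfection, from 15% to 31.5%.** This adds the back-solved 16.5-point margin to the rate and treats the margin as an acceptable observed difference. Noninferiority requires the upper confidence limit to lie below the margin. Against 9/58 in control, with Newcombe limits at one-sided .05, 11/58 passes (upper limit 15.1 points) and 12/58 fails (16.9 points).
- **That 58 came from a superiority calculation.** A two-sided test of 1% against 15% also returns 58, but the 1% is invented, several input pairs return that number, and the article says it used a noninferiority approach.
- **That the interim counts show the margin to be too wide.** The Results section reports "Only 2 patients needed reoperation and only 1 patient needed a change of treatment (antiseptic therapy". These counts are pooled over arms with follow-up incomplete, and reoperation is only one component of the endpoint. They cannot carry such an argument.

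**Conclusion.** The point holds in a limited form. The sample size paragraph gives its only effect input a label that fits neither an expected rate nor a margin. No margin appears in the article, and the sidedness of alpha is not given. The stated inputs used alone lead to 71 or 89 per arm, and 58 is reached only by adding an unstated rate or margin. The 58 per arm and the 80% power are therefore unverifiable, not proven wrong. As this document reads, the primary comparison also lacks a noninferiority criterion.

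This rests on equal true rates in both arms and the normal approximation with unpooled variance. The power figures are illustrations under assumed margins, not properties of the design. It would be wrong to conclude that true power is 73% or 62%, because power is undefined until a margin is stated. The loss allowance is a minor matter and adds nothing to the weight of the point.

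**What to change.** Replace the opening sentence of the Sample Size Calculation section with three stated inputs:
1. the assumed rate of the composite (reinfection or reoperation) in both arms;
2. the absolute noninferiority margin, with its justification;
3. a one-sided alpha.

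Then restate the power that the planned number delivers under those inputs. If a fuller protocol already holds them, carry them over and show that they give 58.

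In the Statistical Analysis section, add that noninferiority will be declared only if the upper confidence limit of the risk difference for the composite endpoint (intervention minus control) lies below that margin, at the stated alpha. Fix and date this before any look at outcomes by arm. With 50 patients enrolled when the article was published, there was room to do so.

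As a minor correction, say that 64 per arm with 10% lost leaves about 57 evaluable per arm.

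The cost is a wording amendment. Enrolment need not rise above 128. The downside is that the stated power may turn out below 80%.
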